# Study Procedures/Evaluations

## Study Procedures

This study’s primary goal is to conduct a randomised controlled trial of intermittent preventive treatment with SP+ AZ (IPTp), compared to single dose curative treatment with SP plus chloroquine in pregnant women using ITNs, delivered through ANCs. The main study outcomes will be evaluated at delivery. Following the intervention women and their children will be followed at 6 weeks and 12 months to measure maternal, neonatal and infant mortality rates. During the antenatal period, women will be followed with passive case detection at participating health facilities.

An overview of the study procedures is provided below and discussed in greater detail in the following subsections.

At first ANC attendance, pregnant women estimated to be between 14 and 26 weeks’ gestation will be invited to join the study. Women presenting in the first trimester ≤13 gestation weeks will be eligible to enter the study and will have blood taken and ultrasound scan performed, but they will be asked to return to receive their initial treatment. Gestation at enrolment will be assessed by ultrasound (when available; primarily at Modilon Hospital), and in its absence by a combination of LMP history from women and abdominal palpation.

At first treatment visit, after informed consent has been obtained, women will be assigned a unique PNGIMR identification number. For each unique identification number, a prepared opaque envelope containing the treatment assignation of that women willl be opened to determine which treatment group she belongs to. Following enrolment a venous blood sample (10 ml) will be collected and the woman will receive the first IPTp treatment. Participants will be provided with a free, long-lasting ITN. Thereafter, the study team will see the woman on one or two further occasions during pregnancy. For women enrolled at or before 26 weeks gestation, they will be seen at two further visits at least 4 weeks apart. At each visit the allocated treatment (SP + AZ at all visits, or SP + CQ at first visit, SP and AZ placebos at subsequent visits) will be dispensed. Only women who spontaneously report illness will undergo an in-depth physical examination. At delivery the mother and her newborn baby will undergo an in-depth clinical examination (including Hb measurement) and a 10 ml venous blood sample will be collected for immunological investigations from mother and from cord blood.

After enrolment, women will attend ANC according to PNG standard recommendations, and their care will be provided by health centre or hospital staff. Women attending for second visit and final visit will receive a further fingerprick blood test, and a further treatment dose. At delivery, a further 10 ml venous blood sample will be taken, either during labour, or within 24 h of delivery. Placental samples and cord blood (from the placental side of the cut cord) for histology, preparation of blood smears and/or immunological studies will be collected. The follow-up of the women will cease at 6 weeks post partum, and of the babies at 12 months post partum. The exception to this is the follow up of 250 women to 3 months post partum for studies of P vivax immunity Schematic representation of study schedules and activities is given in the Study Schedule Diagram in Appendix I

During the entire study period the study will maintain a passive case detection system at participating HCs to detect and treat febrile illness episodes of study women. Active case detection will not be performed.

Ultrasound examinations will be performed on as many women as possible, using a machine based at Modilon Hospital. Standard gestational assessments (biparietal diameter, head and abdominal circumference, femur length) will be performed. At subsequent visits, fetal growth monitoring will be performed, and Doppler flow wave velocimetry (to measure placental blood flow) will be undertaken.

### Field Study Team

The study will be coordinated and day-to-day activities will be carried out by PNGIMR field study teams based at the ANC clinics. The total team is comprised of approximately 21 individuals who live and work in or near the study area. It consists of three study physicians (one expatriate senior physician/field manager, two PNG national), a minimum of 14 nursing officers, 2 microscopists and a laboratory technician. The study physicians and nursing officers are trained specifically to conduct information meetings (“tok saves” in Melanesian Pidgin), recruit participants, and organize and conduct the collection of blood and other measurements based on the research collaborators’ study protocols. Besides organising and supervising the field teams the study physicians are responsible for assuring adequate clinical care of study participants. They will have received appropriate human subjects protections and study conduct training to conduct the study according to good clinical practice (GCP) guidelines. Field study team members routinely work on large-scale malaria research studies that include the collection of blood for archives and laboratory analyses, making blood smears, obtaining haemoglobin concentrations, interviewing study participants, and explaining the results of blood smear and haemoglobin evaluations.

The study team will be supported by a network of village reporters that help the study team communicate with participating villages, assist in follow up of women and children after delivery and encourage women who miss their treatment or follow-up appointments to attend the health centre to make up for the missed visit. Village reporters will also have an important role in detecting out-of-facility deliveries, and ensuring children are weighed within the first 7 days of life.

## Participant Database and Study Visit Activities

After enrolment, the woman’s baseline information will be entered into a participants’ database that will provide scheduling information for subsequent study contacts. As the study will enrol women for 18 months, the study will have an open cohort. The participants’ database will be updated monthly to reflect the status of the cohort through indicators that distinguish women under active follow-up versus women who have delivered (reaching primary study endpoint), and women with completed follow-up or censored from follow-up. The participant database will serve to schedule treatment and follow-up visits for the study participants.

### First contact and pre-screening

The study team will contact potentially eligible women at first ANC visit. The objectives and procedures of the study will be explained and women will be invited to join the study if they are between 14 and 26 weeks pregnant (in which case they will be eligible for treatment that day), or if they are ≤13 weeks pregnant (in which case they will be enrolled, have a finger prick blood sample taken for determination of malarial infections and requested to come back when they reach 14 weeks gestation). Details of eligible women who are in first trimester will be kept in a pre-screening database to ensure they commence treatment at next scheduled visit.

Formal, written informed consent will be obtained at first ANC visit.

### Enrolment and Treatment

1. **Enrolment and 1st Treatment Visit**

Baseline data collection and 1st IPTp treatment will take place at first ANC visit; the exception to this is women in first trimester who will be enrolled at first visit but will only receive first IPTp treatment when they enter second trimester. After consent is obtained, the PNGIMR field study team will conduct the following tasks:

Woman:

- Assess age
- Assess gravidity and parity
- Take anthropometric measurements
  - Weight
  - Height
  - MUAC
- Collect venous blood sample (approximately 10 ml)
  - Prepare thin and thick blood smears
  - Test blood for serological evidence of active syphilis infection by card based RPR test.
  - Archive a portion of the blood sample for laboratory analyses
  - Measure Hb using Hemacue
- Assess for symptoms of severe anaemia, chronic illness or permanent disabilities
- Whenever possible, collect a self-administered high vaginal swab for determination of sexually transmitted infections (STIs)
- Interview and record
  - demographic information (including participant’s date of birth)
  - history of woman’s bednet use in two weeks prior
  - woman’s history of malaria treatment in two weeks prior
- Check the woman’s health records booklet for recent health centre visits and record applicable information
- In women without available date of birth, the age of the woman will be estimated using a calendar of notable local events.
- Book appointment to perform transabdominal ultrasound to measure biparietal diameter, femoral length and abdominal circumference (to estimate gestational age). In women who are ≥24 weeks’ gestation, Doppler studies will be performed, to measure uteroplacental blood flow, and to seek abnormal flow velocity waveforms in the uteroplacental arteries. We expect that this will be performed on all women at Modilon Hospital, but not at all the Health Centres due to logistic constraints.

Data and responses of the woman will be recorded on Enrolment case report forms (CRF) at the time the measurements and interview are conducted. The participant’s health records booklet (if any) will be checked to see if any visits to a health centre have been documented. If the participant has any record of a visit, the field study team will record the date of the most recent visit and any medication the participant received on the Enrolment Form. In women without a health record booklet, a new booklet will be provided free of charge by study staff.

The study team Physician or a trained study team Nursing Officer will assess the woman for sign of chronic illness, symptomatic severe anaemia or permanent disabilities that would preclude her participation into the study. (See 5.2 for list of exclusion criteria). If a woman is excluded on health grounds, she will be referred to nearest health facility for treatment.

Every enrolled woman’s health (record) booklet (already owned, or provided at enrolment) will be clearly marked with a study identifier and study ID number. At any study contact, the study team will record all medically relevant data collected during their examination into the health booklet.

Digital photographs will be taken of participating women at enrolment, and a printed version will be kept in a secure file, for tracking of pregnant women who fail to attend appointments, and to ensure accurate identification of women if required

Following assessment the woman will receive the 1st IPTp treatment dose. The drugs will be dispensed in pre-randomised and pre-numbered Ziploc bags that contain all drugs for initial treatment. The first dose (SP and AZ or SP and chloroquine) will be dispensed directly by the study staff. Pack number, date and time of administration will be recorded on the enrolment forms. The tablets will be administered with water. The woman will then be instructed how to take subsequent AZ or chloroquine doses at home. The woman’s treatment allocation will be noted using randomly-generated codes. Treatment allocation will not be revealed to laboratory staff, and will be kept concealed to the maximum extent possible from other study staff (see 6.3.3.). Senior study investigators will be aware of treatment allocation; hence the study will be single blinded.

A thorough physical examination (including axillary temperature, measurement of Hb etc. will only be conducted on enrolled women who spontaneously report as ill to either the study team or the health centre staff. Women with a presumptive diagnosis of malaria will be tested on the spot for malaria infection using a rapid diagnostic test (RDT). If they have a positive RDT they will be treated with a full course of Coartem and their randomised IPTp treatment (drug or placebo) will be delayed for at least 4 weeks. For all women reported sick, detailed symptomatology, results of RDT and treatments given will be recorded on the ‘Morbidity Surveillance Form’.

At the end of the enrolment visit the study team will schedule the next treatment visit with the woman. Participants will be instructed to seek medical attention immediately if they have any sign or symptoms of illness or any other condition that they deem as a threat to their well-being following the treatment. They will also be encouraged to seek medical care if they note any symptoms of malaria, fever, or illness, and to report any antimalarial treatments received or used.

1. 2nd Treatment Visit

During the 2nd treatment visit the PNGIMR study team will conduct the following tasks:

Woman:

- Interview and record
  - history of bednet use in two weeks prior
  - history of malaria treatment in two weeks prior
- Take growth measurements
  - Maternal weight
  - Fundal height
- Collect 250 µl finger prick blood sample
  - Prepare thin and thick blood smears
  - Archive a portion of the blood sample for laboratory analyses
- Check the woman’s health records booklet for recent health centre visits and record applicable information
- Measure maternal blood pressure and check for oedema. If elevated blood pressure or oedema present, women will be tested for proteinuria. Presence of all three will be considered clinical evidence of pre-eclampsia, and women will be referred for obstetric care through Modilon Hospital.
- If possible, perform second ultrasound examination for fetal growth monitoring.

Data and responses of the participant will be recorded on the 2nd Treatment Visit CRF at the time the measurements and interview are conducted. As at enrolment a thorough physical examination (including axillary temperature, measurement of Hb, etc.) will only be conducted on enrolled women who spontaneously report as ill to either the study team or the health centre staff conducting the clinic. Women diagnosed with presumptive malaria will be tested on the spot for malaria infections using a rapid diagnostic test (RDT). If the RDT is positive, they will be treated with a full course of Coartem instead of the scheduled treatment. For all women reported sick, detailed symptomatology, result of RDT and treatments given will be recorded on the ‘Morbidity Surveillance Form’.

Following the collection of data and blood sample women receiving SP + AZ will receive the 2nd IPTp treatment dose, women in the control arm will receive SP and AZ placebos. The first dose will be dispensed directly by the study staff. Pack number, date and time of administration will be recorded on the enrolment forms. The participant will then be instructed how to take the 2nd dose at home.

At the end of the visit the field study team will schedule the next treatment visit with the woman. Women who failed to attend the study ANC clinic will be contacted by the village reporters and encouraged to present at their health centre to receive the missed treatment.

1. Third IPTp Treatment Visit

During the final treatment visit the PNGIMR field study team will conduct the following tasks:

Woman:

- Interview and record
  - history of bednet use in two weeks prior
  - history of malaria treatment in two weeks prior
- Take growth measurements
  - Maternal weight
  - Fundal height
- Collect 250 µl finger prick blood sample (in first 150 women, collect instead 5 ml venous sample for plasma separation and immunological studies).
  - Prepare thin and thick blood smears
  - Archive a portion of the blood sample for laboratory analyses
- Where possible, collect a self-administered high vaginal swab for determination of sexually transmitted infections (STIs)
- Check the woman’s health records booklet for recent health centre visits and record applicable information
- Measure maternal blood pressure and check for oedema. If elevated blood pressure or oedema present, women will be tested for proteinuria. Presence of all three will be considered clinical evidence of pre-eclampsia, and women will be referred for obstetric care through Modilon Hospital.
- Ultrasound will be performed where available to (a) measure fetal growth using bi-parietal diameter, head circumference, abdominal circumference and femur length and (b) document uteroplacental blood flow patterns using color Doppler, as described

Data and responses of the participant will be recorded on the Final Treatment Visit CRF at the time the measurements and interview are conducted. As at enrolment a thorough physical examination (including axillary temperature, measurement of Hb, etc.) will only be conducted on enrolled women who spontaneously report as ill to either the study team or the health centre staff conducting the clinic. Women diagnosed with presumptive malaria will be tested on the spot for malaria infections using a rapid diagnostic test (RDT). If the RDT is positive, they will be treated according to PNG standard treatment guidelines with a full course of Coartem instead of the scheduled treatment. For all women reported sick, detailed symptomatology, result of RDT and treatments given will be recorded on the ‘Morbidity Surveillance Form’.

Following the collection of data and blood sample the woman will receive the Final IPTp treatment dose (if she is allocated to the SP and azithro arm of the study, or matching SP and Az placebo). Administration will be as for the second treatment dose.

At the end of the visit the field study team will remind the woman of the importance of delivering in the Health Centre or Hospital. Women who fail to attend the study ANC clinic will be contacted by the village reporters and encouraged to present at their local health centre to receive the missed treatment.

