## Treatment & Follow-up Visits

**7.3.1 Treatment Visits**

Following enrolment and 1st treatment women will receive further IPTp treatments at two intervals, at least 4 weeks after the previous administration. For details of procedure see 6.1.4 b & c.

At every ANC visit, only women who spontaneously report illness to study or ANC staff will be assessed on the spot for presence of malaria infections or anaemia.

Women found to have symptomatic severe anaemia (Hb < 6 g/dl) or other severe illness will be referred to the health centre for appropriate treatment. They will not be suspended from participation in the study but will be monitored again for anaemia and clinical status at their next ANC visit. Should their condition not have resolved by that time, they will be considered chronically ill and excluded from further participation in the study.

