**7. 2. 2 Non-treatment ANC visits**

At ANC visits when treatment is not administered, women will be seen by Health Centre/Hospital staff only. Blood pressure, weight, fundal height and other indicators of maternal health will be recorded. Should women have symptoms or signs warranting further investigation, they will be referred to study staff, and an Unscheduled Visit form will be completed. Women with hypertension will have physical examination and urinalysis to seek other evidence of pre-eclampsia. Study or Hospital physicians will assess women as requested by study and health centre nursing staff.

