### Procedures to be followed in the Event of Abnormal Laboratory Test Values or Abnormal Clinical Findings

If a participant is found to have symptomatic severe anaemia (Hb < 6 g/dl with anaemia symptomatology) she will be referred to Modilon Hospital for treatment.

The study coordinator will report such cases as SAE to the PI who will inform the DSMB and MiP SWG.

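### At the second and third treatment visits either of two signs prompts a urine test, but the stated obstetric referral needs all three signs, so proteinuria with only one other sign does not meet it

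*Combined protocol and SAP*

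**What the plan says.** Section 6.1.4 uses the same wording for the second and the third treatment visit. The study team measures blood pressure and looks for oedema. Either sign is enough to test the urine: "If elevated blood pressure or oedema present, women will be tested for proteinuria". The action then depends on the full triad: "Presence of all three will be considered clinical evidence of pre-eclampsia, and women will be referred for obstetric care through Modilon Hospital". Neither visit description says what to do when proteinuria is found with only one of the other two signs.

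Other sections bear on the point:

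- The text on treatment visits in section 7 sends women with symptomatic severe anaemia "or other severe illness will be referred to the health centre for appropriate treatment".
- Section 7.2.2, on antenatal visits without study treatment, says: "Women with hypertension will have physical examination and urinalysis to seek other evidence of pre-eclampsia". It adds: "Study or Hospital physicians will assess women as requested by study and health centre nursing staff".
- Section 9.3.2, on abnormal laboratory and clinical findings, gives one case only, opening "If a participant is found to have symptomatic severe anaemia".
- Section 6.1 says of women attending antenatal clinics after enrolment that "their care will be provided by health centre or hospital staff". The Field Study Team section says that "the study physicians are responsible for assuring adequate clinical care of study participants".
- Appendix II (Clinical Definitions) covers malaria, anaemia and sexually transmitted infections. It does not define pre-eclampsia.

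**The concern.** The test is triggered by one sign or the other, but the action requires both of them plus a positive result. For a woman tested because of a single sign, the urine result therefore cannot change what the stated rule tells staff to do.

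The sentence also goes beyond leaving a gap. It says what counts as clinical evidence of pre-eclampsia, and with no definition in Appendix II it is the only working statement the field team has. A nursing officer following it could reasonably conclude that raised blood pressure with proteinuria, but without oedema, needs no obstetric referral.

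Only the safety of participants is at stake. Pre-eclampsia is not a trial outcome, and the primary comparison, the sample size and the analyses are unaffected.

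**Working it through.** There is no figure in the plan to reproduce. The check lists every combination of signs and applies the two rules in section 6.1.4.

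**Inputs.** B = raised blood pressure, O = oedema, P = proteinuria.

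- Test rule, both visits: test urine if B or O.
- Referral rule, both visits: refer if B and O and P.

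**Combinations.** Three yes/no signs give 2 × 2 × 2 = 8 combinations. Those with B or O number 8 − 2 = 6, because the two without either sign are {none} and {P}. Three of these 6 have proteinuria.

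| Signs that prompted the test | Urine positive: pattern | Meets stated referral? |
| --- | --- | --- |
| B and O | B, O, P | Yes |
| B only | B, P | No |
| O only | O, P | No |

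A positive urine result meets the stated referral in 1 of 3 tested patterns and cannot meet it in 2 of 3. This counts outcomes of the rule. It says nothing about how many women fall in each row.

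**Does another section supply the missing action?**

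- *Treatment visits (section 7).* The route is for severe illness in general, leads to the health centre rather than to obstetric care, and names none of these signs. The same text limits on-the-spot assessment, for malaria or anaemia, to women who report illness themselves. Section 6.1.4 likewise reserves the thorough physical examination for women who report as ill. A woman who feels well would not trigger either.
- *Section 7.2.2.* Hypertension alone leads to examination and urinalysis, with no oedema required. This covers visits without study treatment, states no action on the urine result, and leaves physician assessment to a request.
- *Section 9.3.2.* The only action named is for symptomatic severe anaemia.
- *Sections 6.1, 6.1.7 and 11.3, and Field Study Team.* These place treatment visits within routine antenatal care and assign general responsibility for care. None is a referral trigger.

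**Timing.** Treatment visits are at least 4 weeks apart. In Table 2 the next scheduled study contact after the third treatment visit is delivery. Routine antenatal care continues, but the study itself plans no recheck in between.

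**Same count under the proposed rule.** {B, P} and {B, O, P} are referred (2 of 3). {O, P} is discussed the same day with a study physician (1 of 3). No tested pattern with proteinuria is left without a stated action (0 of 3).

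**The case against.** The strongest reply is that the referral sentence gives a sufficient condition, not an exclusive one. It does not forbid referral of other women, and several routes could catch them. Section 9.3.3 has adverse events managed by best available practice, with the study team providing referral and transport to Modilon Hospital, the same hospital. Section 6.1.4 requires medically relevant findings to be written in the health booklet, so antenatal staff can see the result. Section 7.2.2 shows that the protocol does not treat the triad as the only reason to look for pre-eclampsia. Section 13 leaves field tasks to SOPs that are not in the documents and may say more.

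This limits how often the gap would matter, and it means that nobody can say affected women would go without care. It does not close the gap. Every one of these routes is general or discretionary, and none names these signs as a reason to refer. Section 7.2.2 in fact supports the concern, because there the protocol itself treats hypertension without oedema as grounds to look for pre-eclampsia.

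A second reply is that ranking raised blood pressure with proteinuria above oedema with proteinuria is a clinical judgement without a source in the documents. That is partly fair. Section 7.2.2 supports giving weight to hypertension, but the documents offer nothing equivalent for oedema. The blood-pressure part of the fix is therefore the firmer part, and the oedema part is left to a physician.

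A third reply is feasibility: three study physicians serve seven field sites, and the extra referrals are not sized. This stands as a cost. Physician assessment on request is already provided for in section 7.2.2.

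**Conclusion.** The concern holds for both visits. Section 6.1.4 tests on either sign and refers only on all three, so 2 of the 3 tested patterns with proteinuria, including raised blood pressure with proteinuria, fall outside the only obstetric referral stated for these visits. Followed literally, the rule lets a positive urine test lead to no stated action.

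The conclusion concerns the protocol text only. The number of women affected cannot be estimated, because the documents give no frequency for raised blood pressure, oedema or proteinuria. No harm is shown, and SOPs or routine care may cover these women in practice. No outcome, sample size or analysis changes. It should be corrected because it is a safety rule in pregnant participants and the correction is cheap.

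**What to change.** Keep the test trigger in section 6.1.4. At both visits, replace the referral sentence with text to this effect: *A woman with raised blood pressure and proteinuria, whether or not oedema is present, is sent to Modilon Hospital for obstetric care as possible pre-eclampsia. A woman with oedema and proteinuria but normal blood pressure is discussed the same day with a study physician, who decides on referral.*

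In section 7.2.2, after the sentence on urinalysis for hypertension, add: *If proteinuria is found, she is referred in the same way.*

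This changes who is referred and leaves diagnosis to obstetric care. If only one change is made, it should be referral on raised blood pressure plus proteinuria.

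The cost is one sentence replaced in two places and one sentence added. Blood pressure and oedema are already checked and urine is already tested, so no new measurement is needed. The downside is some extra referrals to Modilon Hospital and some same-day physician discussions, including women who prove not to have pre-eclampsia. Peripheral sites will need a workable way to reach a study physician the same day.

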**Summary**

**In summary, intermittent preventive therapy during pregnancy is gaining popularity as an intervention for mitigation of the devastating impact of malaria on mothers and their babies. This approach needs validation in a variety of settings, especially in areas where there is a high prevalence of non-falciparum infection. We have many years experience in studying the epidemiology of malaria in PNG and the ability to perform clinical trials such as those proposed, together with the infrastructure necessary to perform the supporting laboratory work which will demonstrate whether our intervention may have negative impact on host immunity or parasite resistance.**

We therefore propose a randomized controlled trial to evaluate the efficacy of IPTp with SP (three tablets; 1500 mg/75 mg) plus AZ (2 g daily in divided doses, i.e. 1 g twice daily for 2 days) against a treatment course of SP and chloroquine to prevent LBW in PNG women sleeping under ITNs.

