# Study Design

**The study design of this research project is a randomised placebo controlled single blinded trial in pregnant women enrolled between 14 and 26 weeks’ gestation.** All women participating in this study will be followed until 6 weeks post partum. Infant survival to 1 year of age will be documented.

The intervention consists of three treatment courses of SP (3 tablets: 1500/75 mg) + AZ (2 g/day for 2 days) administered at ANC booking (provided this is between 14 and 26 weeks’ gestation) and at 2 further antenatal visits at least 4 weeks apart. Recipients in the control arm will receive a treatment course of Sp and chloroquine at enrolment, followed by AZ and SP placebos at further treatment time points. All women will be provided with a long lasting insecticide treated bed net. A block randomisation procedure will be used to allocate women to respective control and intervention groups. Among study staff, only those dispensing drug will be aware of subjects’ treatment allocation. At enrolment and at delivery a 10 ml venous blood sample will be collected to determine prevalence of malarial infections and to measure haemoglobin levels, as well as to contribute plasma, serum and peripheral blood mononuclear cells (PBMCs) for immunological analyses. At each subsequent treatment visit a 250µl finger prick blood sample will be collected for retrospective identification of malaria infection status.

At enrolment all women will have blood taken to test for syphilis by RPR and TPHA test, and women with positive tests indicating active or latent syphilis will be treated with benzathine penicillin according to standard treatment guidelines. Women will be asked to self-collect a high vaginal swab, for molecular diagnosis of STIs. Consenting women will also undergo testing for HIV (provided routinely by Modilon Hospital), and infected women will be referred to a local treatment centre providing highly active antiretroviral therapy, for prevention of mother to child transmission, and to maintain health of infected women.

From blood samples collected the prevalence and density of infections will be determined by light microscopy and PCR.

A subset of women who can attend ultrasound clinics at Modilon Hospital will have up to 3 ultrasound scans, to establish gestational age, monitor fetal growth, and measure placental blood flow.

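### The administration text for azithromycin courses 2 and 3 describes two intakes where the Background summary describes four, and no single meaning of dose fits all the sections

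*Combined protocol and SAP*

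**What the plan says.** The AZ regimen is described in several places.

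- **Background Information, Summary:** "AZ (2 g daily in divided doses, i.e. 1 g twice daily for 2 days".
- **Study Design:** "three treatment courses of SP (3 tablets: 1500/75 mg) + AZ (2 g/day for 2 days". This applies one daily amount to all three courses and does not say whether it is divided.
- **Section 6.1.4, enrolment and first treatment visit:** staff give a first dose, and then "The woman will then be instructed how to take subsequent AZ or chloroquine doses at home". The plural carries no number.
- **Section 6.1.4, second treatment visit:** "The first dose will be dispensed directly by the study staff". Next comes "The participant will then be instructed how to take the 2nd dose at home", in the singular. Women in the control arm receive SP and AZ placebos under the same text.
- **Section 6.1.4, third treatment visit:** "Administration will be as for the second treatment dose".

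On packs, section 6.1.4 says that the bag for the first course holds all the drugs for that course. Section 6.3.2 says that drugs and placebos are pre-packed in coded bags. Neither gives a tablet count for courses 2 and 3.

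**The concern.** The second-visit wording is the protocol's instruction for giving the experimental drug at two of the three courses, and it does not match the regimen stated earlier. On the Background description, three of the four intakes in a course are taken at home, so most of the course depends on what the woman is told. With 7 field sites and at least 14 nursing officers, the wording could be read differently from place to place.

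A difference in reading would be hard to see afterwards. The task lists for the second and third visits include no tablet count or check of home doses. Their interview on malaria treatment looks back two weeks, while courses are at least four weeks apart. The planned covariate in section 11.4.1 is the number of IPTp treatments received, not the amount taken.

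What is at stake is whether the trial's conclusion on low birth weight and malaria belongs to the regimen that the protocol names. The Background treats total dose as relevant: it reports greater benefit in non-pregnant adults at 3 g in total, and the two candidate course totals, 2 g and 4 g, lie on either side of that figure.

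**Working it through.** **Step 1. The stated course.**

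- Background summary: 1 g × 2 per day × 2 days = 4 g, in 2 × 2 = 4 intakes.
- Study Design: 2 g per day × 2 days = 4 g. The number of intakes is not stated.

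The two agree on the total. Over three courses it is 3 × 4 g = 12 g.

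**Step 2. What the visit text describes.**

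- Course 1: one intake with staff, then an unstated number at home. This is compatible with 4 − 1 = 3 home intakes. The plural also covers chloroquine, so it is only supporting evidence.
- Course 2: one intake with staff and one at home, 1 + 1 = 2 intakes. No grams are stated.
- Course 3: as course 2, by cross-reference.

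**Step 3. Each meaning of dose for courses 2 and 3.**

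| Meaning of dose | Course total | Share of 4 g | Conflict |
| --- | --- | --- | --- |
| 1 g, the divided amount | 2 × 1 g = 2 g | 50% | With the 4 g in both the Background summary and Study Design |
| A day's 2 g | 2 × 2 g = 4 g | 100% | With the Background summary, because 2 g is taken at once instead of 1 g twice |

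Suppose instead that dose means a day's amount and only 1 g of it is taken at the visit. Three 1 g intakes then remain for home, and the instruction does not describe them.

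Dose is also used for a whole course, as in "women receiving SP + AZ will receive the 2nd IPTp treatment dose". That meaning cannot apply to the two administration sentences, because a first course given by staff would leave nothing of that course to take home.

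**Step 4. Over three courses, taking course 1 as the full 4 g.**

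- 1 g meaning: 4 + 2 + 2 = 8 g of 12 g (67%).
- Daily meaning: 4 + 4 + 4 = 12 g of 12 g (100%).

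These are the ends of the range that the text allows. Neither is a forecast of what women would take.

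**The case against.** The strongest answer is that the regimen itself is stated consistently. The Background summary and Study Design agree on 4 g per course, and nowhere is a 2 g course prescribed. With Study Design's "AZ (2 g/day for 2 days" in mind, the first and second doses are naturally day 1 and day 2, and the full 4 g is given. Dose is used loosely throughout, so a singular noun is weak evidence of a different regimen. Bags are pre-packed, so the amount handed over need not depend on this sentence. Section 13 says that tasks will be set out in SOPs, which may specify the course.

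Much of this stands. A reader might infer that courses 2 and 3 deliver half the stated amount, or that a 33% shortfall over pregnancy (4 g of 12 g) is to be expected. The documents do not support that: it needs the 1 g unit to be read into a sentence that gives no grams, and nothing shows that a later bag holds 2 g.

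Three further inferences should also be resisted.

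- **Weaker effect on sexually transmitted infections.** The Background says that 2 g or less cures syphilis, gonorrhoea and chlamydia, so even the lower reading does not imply this.
- **A problem with replacing vomited drug.** Section 6.3.2 replaces drug vomited within 1 hour whatever the amount, and neither reading changes that rule.
- **Every woman affected at two courses.** Section 6.1 allows one or two further contacts, section 6.2.3 has a third dose only where applicable, and women with a positive rapid test receive Coartem instead of the scheduled treatment.

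The objection does not remove the conflict. The day 1 and day 2 reading keeps the total only by setting aside the divided dosing in the Background summary. Pre-packing does not resolve it either, because the later bag contents are unstated and the woman still needs a correct home instruction. SOPs may be clear, but they should not have to correct the protocol.

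**Conclusion.** The inconsistency is real and should be corrected. Two intakes in section 6.1.4 stand against four in the Background summary. The text for courses 2 and 3 accounts for either 2 g or 4 g of the stated 4 g, depending on what a dose is, and neither meaning satisfies all the sections.

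This assumes that dose has the same meaning in the two consecutive sentences on the second course, and that the first dose is taken at the visit, where the date and time of administration are recorded.

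No size can be put on any effect on birth weight or malaria. The documents do not show which reading sites would adopt, and they give no dose-response figure for this use. The point is one of internal consistency, not a fault in the choice of design. It does not touch the sample size and implies no view on which regimen is right.

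**What to change.** Reconcile the Background summary, Study Design and the three treatment-visit descriptions in section 6.1.4, so that one description of the AZ course, and of the matching placebo, applies wherever it is given. It should state:

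- what a dose means, kept distinct from a course;
- the number of intakes and the amount of each;
- which intake staff give;
- how many intakes are taken at home.

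State the bag contents for courses 2 and 3 in section 6.3.2, and make the participant instruction match. The sponsor decides which description is intended.

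The cost is wording in the protocol and in the dispensing procedures. It needs no additional women or visits.
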